# 0 reading represents “no pain”

# 3 readings represent “mild pain”

# 4- 6 readings represent “moderate pain”

# 7- 10 readings represent “severe pain”

Secondary outcomes will be collected by the operator by commercial standard kit then stored at -80^0^ C so that all samples would be processed at the same time by LAL assay for quantification of bacterial endotoxins.

- **Statistical analysis:**

Data will be analyzed using IBM SPSS advanced statistics (Statistical Package for Social Sciences), version 21 (SPSS Inc., Chicago, IL). The level of endotoxins will be described as mean and standard deviation. The level of pain will be described as median and range or interquartile range, as appropriate. The level of endotoxins will be explored for normality using Kolmogrov-Smirnov test and Shapiro-Wilk test. If the exploration of data reveals that the collected values are normally distributed, a 2-way ANOVA with repeated measures will be performed to compare between the 2 groups and the change with time. If the interaction between the groups and time is found to be significant, a 1-way repeated measures ANOVA will be used to examine significant differences between time periods within each of the two groups. The Student’s t-test will be performed to test the significance between the two groups at each time period. If the exploration of data reveals that the level of endotoxins is not normally distributed and for the analyses of the pain score, Mann-Whitney U test will be performed to test the significance between the 2 groups at each time period. Friedman’s test followed by multiple comparisons test will be performed to test the significance between the 4 time periods within each group. In addition, correction of p-value will be done using Bonferroni adjustment to avoid hyperinflation of type 1 error that arises from multiple comparisons. A p-value less than or equal to 0.05 will be considered statistically significant. All tests will be two tailed. The effect size will be measured using standardized mean difference.

- **Data monitoring:**

There will not be a Data Monitoring Committee for the following reasons:

- Interim analysis is not involved in the trial so periodic inspection of the accumulating outcome data is not required.
- Short duration of the trial.
- Minimal risks of the trial.
- **Harms**

Adverse events are minimal or rare. However, if any harm is seen in the participants either in intervention or control groups they will be recorded and reported at the end of the trial. It will be documented as part of routine monitoring not as outcome. The treatment will be according to the harm:

- Pain: administration of Analgesics.
- Swelling: hot fomentation, mouth rinse with salty warm water, antibiotic will be administrated.
- Allergic reaction: referral for a physician for corticosteroid therapy.
- Auditing

In this trial, auditing will be performed in order to preserve the integrity of the trial, the audit will review the processes of participant enrolment, consent, eligibility, allocation to study groups and adherence to trial interventions and policies to protect participants.

- **Ethics and dissemination**
- **Research ethics approval:**
- This protocol and the template informed consent form will be reviewed by the Ethics Committee of Scientific Research, faculty of oral and dental medicine, Cairo University.
- Each of the protocol, informed consent forms in Arabic and English language, recruitment materials and any modifications will be done later on also will be reviewed and approved by the ethical review Committee.
- **Protocol amendments:**

The ethical committees will notified any administrative changes or modifications of the protocol or modification of registered online protocol.

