**O: outcomes:**

|  | **Outcome measure** | **Tool for measurement** | **Unit of measurement** |
| --- | --- | --- | --- |
| Primary | Postoperative Pain | Numerical rating scale (Brunelli et al, 2010) | Ordinal |
| Secondary | Quantification of endotoxins | LAL assay | EU/mL |

Postoperative pain will be measured using Numerical Rating Scale (NRS) after 6, 12, 24 and 48 hours from the end of root canal obturation **(Evaristo et al. 2013)**

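### Endotoxin is summarised only by mean, SD and standardized mean difference, even where the protocol's normality rule sends it to rank tests (minor)

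*Protocol*

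**What the plan says.** All but one of the relevant statements are in one paragraph of the protocol, under Statistical analysis.

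- Summary of endotoxin: "The level of endotoxins will be described as mean and standard deviation". No condition is attached.
- Summary of pain, in the next sentence: "The level of pain will be described as median and range or interquartile range, as appropriate".
- Normality check: "The level of endotoxins will be explored for normality using Kolmogrov-Smirnov test and Shapiro-Wilk test". No transformation is mentioned.
- If endotoxin is normal: two-way repeated-measures ANOVA, with t-tests between groups at each time.
- If it is not: "the level of endotoxins is not normally distributed and for the analyses of the pain score, Mann-Whitney U test will be performed" between groups at each time. Within groups, "Friedman’s test followed by multiple comparisons test will be performed to test the significance between the 4 time periods within each group".
- Effect size: "The effect size will be measured using standardized mean difference". No rank-based alternative is given.

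The remaining statement is the outcomes table, whose endotoxin row reads "Quantification of endotoxins | LAL assay | EU/mL". That is the only scale given.

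**The concern.** The plan has two branches for testing endotoxin but only one way of describing it. For pain, which always goes to rank tests, it chooses a median with range or interquartile range. It therefore matches summary to test for one outcome and not for the other.

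If endotoxin fails the normality check, the results table would show arithmetic means, SDs and a standardized mean difference beside a p-value from a test that uses none of them. A concentration in EU/mL cannot be negative and may be right-skewed, and then one or two high canals can dominate the mean and inflate the SD. A reader could see a significant p-value next to figures that do not appear to support it, with no estimate of the contrast that was tested. Endotoxin is the only secondary outcome and is named in the trial's aim.

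**Working it through.** **1. Text, side by side**

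| Outcome and branch | Test between groups | Summary | Effect size |
|---|---|---|---|
| Pain | Mann-Whitney | median, range or IQR | standardized mean difference |
| Endotoxin, normal | ANOVA, t-test | mean, SD | standardized mean difference |
| Endotoxin, not normal | Mann-Whitney | mean, SD | standardized mean difference |

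The last row is the mismatch. It follows from the wording alone.

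**2. Inputs for its size**

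- From the protocol: 36 patients, 1:1, losses of about 25%, two-sided 5% level. 36 × 0.75 = 27 completers, taken as 14 and 13.
- Assumed, because the protocol gives no endotoxin mean, SD or expected difference: lognormal EU/mL, a true geometric-mean ratio of 0.4, and an SD of ln(EU/mL), called s, from 0.5 to 1.5.

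The plan has no endotoxin figure of its own to reproduce.

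**3. What the displayed figures imply**

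For a lognormal variable, mean/median = exp(s²/2). This gives exp(0.125) = 1.13, exp(0.32) = 1.38, exp(0.5) = 1.65 and exp(1.125) = 3.08 for s = 0.5, 0.8, 1.0 and 1.5.

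With arms of fixed size, the standardized mean difference d determines the raw-scale t statistic: t = d × √(n₁n₂/(n₁+n₂)) = d × √(182/27) = 2.596 d. The two-sided 5% critical value on 25 degrees of freedom is 2.060, so a d below 2.060/2.596 = 0.79 has an interval that includes zero. The raw-mean comparison is thus what a reader can reconstruct from the table, although the plan would not run it in this branch.

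**4. Simulated results** (thousands of trials per setting; repeat runs differ by up to about two percentage points)

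| s | Shapiro-Wilk rejects in at least one arm | SD exceeds mean in at least one arm | Mann-Whitney significant, raw-mean comparison not |
|---|---|---|---|
| 0.5 | 57% | 1% | about 1% |
| 0.8 | 86% | 32% | about 12% |
| 1.0 | 95% | 68% | about 19% |
| 1.5 | almost 100% | 98% | about 19% |

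Among trials that fail Shapiro-Wilk and have a significant Mann-Whitney test, the raw-mean comparison is not significant in about 34% (s = 1.0) to 64% (s = 1.5).

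**5. Two checks on how far this goes**

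- Direction: means pointing against a significant Mann-Whitney test occur in 0.1% (s = 1.0) to about 0.5% (s = 1.5) of all trials.
- Power: the plan's two-branch rule has 60% (s = 1.0) and 32% (s = 1.5). A t-test on the log scale has 61% to 63%, and 34%.

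**The case against.** The strongest reply is that this is a wording gap on a secondary outcome. Mean and SD are not false figures, and nothing forbids adding a median. The mismatch exists only if the normality check fails. Every percentage above rests on an assumed distribution, and at s = 0.5 the conflict all but disappears. All of this stands, and it sets the severity.

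It does not remove the point. The protocol is not silent in a way that a statistical analysis plan could be presumed to fill: it positively names one summary and one effect size and leaves both unconditional.

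Three stronger readings are tempting, and the documents support none of them.

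- *Power is lost by analysing skewed data on the raw scale.* A raw t-test does do much worse than a log-scale one (about 44% to 46% against 63% at s = 1.0). But the protocol sends data that fail the normality check to Mann-Whitney, so skewed data seldom reach the t-test. Under the rule as written the loss is about 1 to 3 points.
- *The means may contradict a significant rank test in direction.* This is possible but rare. Raw means oppose the ranks in 2% to 11% of all trials at s = 1.0 to 1.5, but almost all of those trials have a non-significant rank test.
- *Endotoxin must be analysed on the log scale.* The choice of scale is open. The inconsistency can be cured without it.

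**Conclusion.** The point holds as an internal inconsistency of minor severity. In the non-normal branch the endotoxin summary and effect size do not describe the contrast being tested. Under the stated assumptions (lognormal, ratio 0.4, 14 versus 13), a significant Mann-Whitney result would sit beside a non-significant raw-mean comparison in about 1% of trials at s = 0.5, 12% at 0.8 and 19% at 1.0 to 1.5. The true spread is unknown, so no single figure in that range can be claimed.

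A reader might infer that the endotoxin test itself, or the trial's main conclusion, is compromised. Neither follows: the p-value and type I error of the rank test do not depend on how the data are described, and the primary outcome is pain, which already has a median-based summary. What suffers is the interpretability of the secondary outcome's reported figures.

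**What to change.** Tie the summary to the branch. Suggested text: *Endotoxin: mean and standard deviation if normally distributed; otherwise median and interquartile range per group, with the Hodges-Lehmann difference between groups and its 95% CI.* Limit the sentence on the standardized mean difference to the normal branch. Changing only the first sentence would leave a mean-based effect size next to the rank test.

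The cost is two edited sentences, with no new data, no change of test and no change of sample size. It should be done before the data are unblinded, so that the summary is not chosen after seeing the results.

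An acceptable alternative is to analyse log10(EU/mL) and report geometric means and their ratio with a 95% CI. This costs slightly more: a substitute value for readings below the assay limit must be fixed in advance, and the normality check must be reworded to apply to the log values.

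### Two normality tests on the trial's own data choose the between-arm endotoxin test, with no rule if they disagree and no deciding time point named

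*Protocol*

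**What the plan says.** The outcomes table lists endotoxin as the secondary outcome: "Quantification of endotoxins | LAL assay | EU/mL". Under Statistical analysis the Protocol states that "The level of endotoxins will be explored for normality using Kolmogrov-Smirnov test and Shapiro-Wilk test". What follows depends on the result.

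- **If the values look normal:** "a 2-way ANOVA with repeated measures will be performed to compare between the 2 groups and the change with time". A significant interaction leads to within-arm repeated-measures ANOVAs. For the arms, "The Student’s t-test will be performed to test the significance between the two groups at each time period".
- **If they do not:** "Mann-Whitney U test will be performed to test the significance between the 2 groups at each time period". Within arms, "Friedman’s test followed by multiple comparisons test will be performed to test the significance between the 4 time periods within each group".

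Whichever branch is taken, "The level of endotoxins will be described as mean and standard deviation", and the effect measure is a standardized mean difference. A Bonferroni correction is announced without its family. Significance is two-sided at 5%.

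The procedural steps give three endotoxin samples: on access, after preparation, and after 7 days of medication. The first two precede the medication.

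**The concern.** The rule makes the analysis depend on the data it will analyse, and it cannot always be carried out in one way, because two normality tests are named and nothing says which prevails.

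The branches also differ in what they test. The normal branch compares means and, through the interaction, asks whether change over time differs between arms. The other compares ranks at separate times and has no between-arm test of change.

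Either way, comparisons are made at every sampling time with none designated as decisive. Two of the three samples precede the medication and cannot show its effect. Reducing endotoxin is one of the two goals in the aim and research question, so a reader should know beforehand which comparison answers it.

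**Working it through.** **Inputs from the Protocol (Sample Size; procedural steps).** Total 28 before losses and 36 after, allocated 1:1, so 28/2 = 14 and 36/2 = 18 per arm. Three samples in two arms give 3 × 2 = 6 cells. The Protocol gives no endotoxin distribution and no power figure for endotoxin.

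**The plan's own figure.** The base total of 24 reproduces if effect size f = 0.25 is read as a repeated-measures effect with 4 measurements and correlation 0.5 (both assumed): λ = f²·N·m/(1 − r) = 0.0625 × 24 × 4 / 0.5 = 12, on 3 and 3 × 22 = 66 degrees of freedom, power 0.816. It is not in dispute and serves only to fix the arm sizes.

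**Assumptions for the simulations.** Correlation 0.5 between samples. Data are normal, or log-normal with log SD 0.3, 0.5 or 0.8. Each cell is tested at 5% with Shapiro-Wilk and with Kolmogorov-Smirnov (Lilliefors-corrected), and one rejection in any of the six cells leaves the normal branch. The day-7 effect is 0 or 1 SD (log scale for the log-normal data). Tests are unadjusted at 5%.

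**Step 1: how often a gate misfires on normal data.** With six independent cells, 1 − 0.95⁶ = 0.265. Simulation with correlated samples gives about 25 to 28% for either test.

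**Step 2: how often the two tests split.** With normal data they disagree in 5.2% of single cells at 14 per arm and 4.6% at 18. The chance of at least one disagreement in six independent cells is 1 − 0.948⁶ = 0.27 and 1 − 0.954⁶ = 0.25. This is a ceiling, since a cell-level disagreement need not change the branch. Simulated branch disagreement:

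| Data | Different branch chosen |
|---|---|
| Normal, or log SD 0.3 | 21–29% |
| Log SD 0.5 | 11–17% |
| Log SD 0.8 | under 3% |

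**Step 3: whether the tests ask the same question.** Take two log-normals with equal medians and log SDs 0.5 and 1.2. Means are exp(σ²/2): exp(0.125) = 1.13 and exp(0.72) = 2.05. At 18 per arm the t-test rejects in about 12% of trials and Mann-Whitney in about 5%. The targets differ, though in this example the practical gap is small.

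**Step 4: whether verdicts differ (1 SD day-7 effect).**

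| Comparison | Opposite verdicts | Normality tests split and verdicts differ |
|---|---|---|
| Day-7 t-test v. day-7 Mann-Whitney | 5–18% | at most about 2% |
| Interaction v. day-7 Mann-Whitney | 19–52% | at most about 9% |

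**Step 5: type I error, no true effect.**

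| How the rule is used | Error |
|---|---|
| One normality test, applied mechanically | near 5% |
| Better of day-7 t-test and Mann-Whitney | about 6–7% |
| Interaction may also be chosen | about 7–10% |

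If the choice is free only when the normality tests split, the figure for one t-test or Mann-Whitney comparison is at most about 6.0%.

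**Step 6: power at 14 per arm.** A fixed day-7 t-test on logs has 71 to 73%. A Shapiro-Wilk gate between day-7 t-test and Mann-Whitney has 68 to 70%. The fixed test gains about 1 to 4 points. Adjusting for the second sample multiplies the residual variance by 1 − 0.5² = 0.75, and the gain becomes about 10 points or more.

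**The case against.** The best reply is that the comparison is already fixed and only the test statistic is left open. Both branches compare the arms at each time period. That is right. A reader might infer that no endotoxin contrast is pre-specified at all, but the text does not support this. The lack of a single deciding time point is a separate gap, and settling the normality rule alone would not close it.

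A reader might also take the large discordance and the error of up to 10% as the cost of the gate. Those figures set the interaction against a day-7 Mann-Whitney, and the Protocol nowhere makes the interaction the deciding test. Like for like, the numbers are much smaller. The extremes also do not coincide: discordance is greatest at log SD 0.8, where the normality tests almost always agree on the branch.

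Three further points stand. The significance level of the normality tests and the unit they apply to are ordinary SAP detail and are not counted here. The simulations ignore the announced Bonferroni correction, whose family is unstated. The Protocol gives no EU/mL distribution, so skewness is an assumption, and the log scale is a sensible choice but not the only one.

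What remains is that the Protocol itself states a data-dependent rule that has no single outcome when its two tests disagree.

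**Conclusion.** The point holds as a minor one. The choice of endotoxin test is left to two normality tests with no tie-break, the interaction exists in one branch only, and no deciding time point is named. At 14 to 18 per arm the tests would choose different branches in about 11 to 29% of trials for data from normal to log SD 0.5, and in under 3% at log SD 0.8. These rates rest on the assumed correlation of 0.5 and the any-of-six-cells reading of the rule.

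The documents do not support reading this as a doubled false-positive rate: a mechanically applied gate stays near 5%, and the higher figures need a free choice of test. Nor is the main conclusion at risk, because Mann-Whitney is fixed for pain without any gate.

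Two smaller mismatches have the same source. Mean, SD and standardized mean difference are kept even when the test is rank-based. The four periods given for Friedman's test do not fit three endotoxin samples.

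**What to change.** In Statistical analysis, remove the normality tests as the selector for endotoxin and name one between-arm contrast:

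- **Main analysis:** log10(EU/mL) of the third (day-7) sample, compared between arms, preferably by ANCOVA with the log10 second (pre-medication) sample as covariate. Report a ratio of geometric means with 95% confidence interval, whatever the data look like.
- **Sensitivity analysis:** Mann-Whitney on the same day-7 sample.
- **Descriptive only:** the other time points and all within-arm tests, with the number of endotoxin samples corrected to three.

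This takes a few sentences and needs no extra patients, samples or assays, since the covariate is already collected. The downsides are small. Results are ratios rather than differences in EU/mL, and values below the assay limit need a substitution rule fixed in advance. The gain from the covariate depends on the actual correlation between the two samples.

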A 2-stage access cavity preparation will be performed. The first stage involved the removal of caries without exposure of the pulp chamber by using a high-speed diamond bur. In the second stage, before entering the pulp chamber, the access cavity will be disinfected according to the decontamination protocol described previously. A new bur will be used to access the canal.

1. 1^st^ sample:-

The first endotoxin sample will be taken by introducing the paper points^[[2]](#footnote-2)^ into the full length of the canal (determined by radiographs and apex locator^[[3]](#footnote-3)^) and retaining them in position for 60 seconds. Next, the paper points will be placed in a glass tube and stored at -80^0^C for the LAL assay.

1. Preparation:-

-The root canals will be prepared with Gates-Glidden drills^[[4]](#footnote-4)^ sizes 4, 3 and 2 for the coronal part, and rotary Irace instruments^[[5]](#footnote-5)^ using an endodontic motor^[[6]](#footnote-6)^ with adjusted torque and speed according to the manufacturer's instructions. The rotary files will be introduced inside the canal using EDTA gel^[[7]](#footnote-7)^.

-Before the use of each instrument, irrigation with a syringe (27-G needle) Containing 3ml 2.5% sodium hypochlorite^[[8]](#footnote-8)^.

- Subsequently, 5% sodium thiosulfate will be used to inactivate NaOCl. Then, 5ml saline solution to wash the canal.

1. 2^nd^ sample:-

The second endotoxin sample will be taken as previously described just after the irrigation with saline solution.

1. Intracanal medication:-

The canals will be dried with paper points and filled with intracanal medication plugged into the canal by using Lentulo spiral^[[9]](#footnote-9)^ . The access cavities will be properly filled with Cavit^[[10]](#footnote-10)^.

- **Control group:** Ca (OH)_2_ Paste.
- **Experimental group:** antibiotic paste (ciprofloxacin, metronidazole)

1. The patient will be instructed to record his/her pain level on the pain scale chart after 6 h, 12 h, 24 h and 48 h.
2. 3^rd^ sample:-

After 7 days of intracanal medication, the canal will be accessed under rubber dam isolation by using the protocol for disinfection described previously. The medication will be removed, the final endotoxin sample will be taken just after the irrigation with saline solution.

1. Obturation:-

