# 0 reading represents “no pain”

# 3 readings represent “mild pain”

# 4- 6 readings represent “moderate pain”

# 7- 10 readings represent “severe pain”

- **Secondary Outcomes:**

The quantitative limulus amoebocyte lysate (LAL) test was used to measure endotoxin concentrations in the root canals by a commercial standard kit. The LAL assay is highly sensitive for detection of minute concentrations of endotoxin. LAL is an aqueous extract of blood cells (amoebocytes) from the horseshoe crab, Limulus polyphemus, that reacts with bacterial endotoxin or LPS. This reaction is the basis of the LAL test, which is used for the detection and quantification of bacterial endotoxins.

- **Participant timeline:**

1. Patients will be selected from the clinic of endodontic after eligibility.
2. They will be randomized and pretreatment diagnosed and radiographed at the same visit of treatment.
3. Patients will be treated in two visits and will record preoperative and postoperative degree of pain at 6, 12, 24 and 48hrs.
4. Patients will return pain charts to the operator on the second visit.

| **periods** | **Recruitment** | **Diagnosis** | **Periapical radiograph** | **Randomization** | **Follow up for postoperative pain** |
| --- | --- | --- | --- | --- | --- |
| Zero |  |  |  |  |  |
| 6 h |  |  |  |  |  |
| 12 h |  |  |  |  |  |
| 24 h |  |  |  |  |  |
| 48 h & close out |  |  |  |  |  |

- **Sample Size:**

The aim of this study is to compare the ability of antibiotic paste versus calcium hydroxide used as intra-canal medication in reducing pain and level of endotoxins in necrotic teeth with apical periodontitis. Based on previous study by Ehrmann, et al. (2003), a medium effect size of approximately 0.25 is expected. A total sample size of 24 patients will be sufficient to detect an effect size of 0.25, a power of 80%, and a significance level of 5%. This number has been increased to a total sample size of 28, to adjust for using nonparametric tests. The number is again increased to a total sample size of 36 (18 in each of the two groups) to allow for losses of around 25%. Sample size was calculated using G*Power program (University of Düsseldorf, Düsseldorf, Germany)^[[13]](#footnote-13)^ . minimal clinical difference 3.5 and 4.5 at 24 hrs and 48 hrs respectively.

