# Recruitment:

Patients are recruited for our clinical trial from the clinic of endodontic at the faculty of oral and dental medicine, Cairo University to meet the target sample size.

- **Randomization:**

1. **Sequence generation :**

A random sequence will be generated by computer software,

(http://www.random.org/).

The table will be kept with the assistant supervisor.

1. **Allocation concealment mechanism :**

- Eight folded numbered papers will be packed in opaque sealed envelopes to be dragged by the patients.
- After instrumentation, operator will open the envelope and use the intra-canal medication assigned to that patient. The opaque envelopes will contain the numbers of each random sequence for both groups (AP for experimental group) and (Ca (OH)_2_ for control group).

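### Only the day-7 endotoxin sample can show a medication effect, yet the groups are tested at every sample and day 7 is never adjusted for the pre-medication level

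*Protocol*

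**What the plan says.** The procedural steps in the Protocol give three endotoxin samples. The first follows access, before preparation. For the next, "The second endotoxin sample will be taken as previously described just after the irrigation with saline solution", which ends the preparation step. The medication is then placed, and the last sample is taken after it has been in the canal for 7 days. On allocation, the Allocation concealment mechanism section says: "After instrumentation, operator will open the envelope".

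In the Statistical analysis section, if endotoxin looks normally distributed, "a 2-way ANOVA with repeated measures will be performed to compare between the 2 groups and the change with time". A significant group-by-time interaction leads to within-group ANOVAs, and Student's t-test compares the groups at each time. If endotoxin is not normal, and for pain in any case, Mann-Whitney compares the groups at each time, and Friedman's test is used to "test the significance between the 4 time periods within each group". Bonferroni is named without saying which tests form the family. No stated analysis uses an earlier endotoxin sample as a covariate.

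**The concern.** The medication cannot affect a sample taken before it is placed. At samples 1 and 2 the null hypothesis of no medication effect is true by design, so a significant between-group result there could only be chance. These samples are useful as a measure of each canal's starting level, and sample 2 is the closest to the start of the medication. The plan uses them as outcome times instead.

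The day-7 t-test ignores the starting level. The interaction allows for earlier levels only through change, with no estimated regression weight, and spreads a single effect over two numerator degrees of freedom. In the non-normal branch, the only between-group test is an unadjusted Mann-Whitney.

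At stake is precision on the only stated secondary outcome in a trial of 36 patients. In addition, the four periods in the Friedman sentence fit the postoperative pain times but not three endotoxin samples.

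**Working it through.** **1. Timing.**

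| Sample | When taken | Randomised medication in place? |
|---|---|---|
| 1 | After access, before preparation | No |
| 2 | After preparation and saline wash | No |
| 3 | Day 7, after the medication is removed | Yes, for the preceding 7 days |

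**2. The plan's own sample size.** The Sample Size section says: "A total sample size of 24 patients will be sufficient to detect an effect size of 0.25, a power of 80%, and a significance level" (the level is 5%). It does not give the number of measurements or their correlation. Reading 0.25 as Cohen's f in a repeated-measures ANOVA with two groups, correlation 0.5 and sphericity (all assumed), the noncentrality is λ = N f² m/(1 − ρ).

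- m = 4: λ = 24 × 0.0625 × 4/0.5 = 12, power 81.6%. This reproduces 24.
- m = 3, as for endotoxin: λ = 24 × 0.0625 × 3/0.5 = 9, power 74%. N = 28 gives 81%.

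The total of 24 therefore fits four measurements. The Protocol next says: "This number has been increased to a total sample size of 28, to adjust for using nonparametric tests". I use 28/2 = 14 per arm as the evaluable number, and 18 per arm as the number if nobody is lost.

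**3. False positives at samples 1 and 2.** With each tested at 0.05 and independence, 1 − (1 − 0.05)² = 0.0975. Positive correlation lowers this. Simulation with correlations from 0 to 0.7 gave about 8–10%, and a second run gave 7–10%.

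**4. Power at day 7.** The documents give no endotoxin SD, effect or correlation, so the values below are assumptions. Values are normal on the log scale with unit SD, the effect is at sample 3 only, and α is 0.05 two-sided with no Bonferroni division. ANCOVA multiplies the residual variance by 1 − R².

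*Effect 0.9 SD, 14 per arm, ANCOVA on both earlier samples, 3,000 trials per scenario. A range shows separate runs. The Monte Carlo standard error near 70% is √(0.7 × 0.3/3000), about 0.8 points.*

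| Correlations S1–S2 / S2–S3 / S1–S3 | Interaction | Day-7 t-test | ANCOVA |
|---|---|---|---|
| 0.1 / 0.1 / 0.1 | – | 64% | 60% |
| 0.3 / 0.3 / 0.2 | 47–48% | 64% | 63–65% |
| 0.5 / 0.5 / 0.3 | 57–59% | 63% | 71–72% |
| 0.5 / 0.7 / 0.4 | 71% | 64% | 86–88% |
| 0.7 / 0.7 / 0.7 | 89% | – | 92% |

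An uncorrected day-7 Mann-Whitney has 58–59%.

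Sample 2 carries most of the gain. At 0.5/0.5/0.3, sample 2 alone gives R² = 0.5² = 0.25. Both samples give (0.25 + 0.09 − 2 × 0.5 × 0.3 × 0.5)/(1 − 0.25) = 0.19/0.75 = 0.253. Sample 1 adds more only when it correlates with day 7 as strongly as sample 2 does. At 0.7 throughout, R² is 0.49 for sample 2 alone and (0.98 − 0.686)/0.51 = 0.576 for both.

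*Effect 1.0 SD, equal correlations, ANCOVA on sample 2 alone, 20,000 trials per scenario:*

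| Per arm | ρ | Interaction | Day-7 t-test | ANCOVA |
|---|---|---|---|---|
| 14 | 0 | 45% | 72% | 70% |
| 14 | 0.3 | 61% | 72% | 75% |
| 14 | 0.5 | 76% | 72% | 82% |
| 14 | 0.7 | 94% | 72% | 94% |
| 18 | 0.5 | 87% | 83% | 91% |

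Each planned test does well in part of the range. ANCOVA is at or near the best throughout.

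**The case against.** The strongest reply is that the plan already tests the medication effect. The interaction and the day-7 t-test both address it, the extra tests at samples 1 and 2 do not bias the day-7 result, and a repeated-measures ANOVA with tests at each time is valid. All of this stands. The gain from adjustment also depends on correlations that the documents do not give, and at ρ = 0 the t-test is marginally better (72% against 70%). Covariates are often left to an analysis plan, but this section already fixes the models and tests, so it can be judged as written.

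A reader might infer more than the text supports:

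- *That the ANOVA assumes four periods.* Its sentence gives no number. Four appears only in the Friedman sentence, shared by pain and non-normal endotoxin. The mismatch is confined to that branch.
- *That the non-normal branch ignores the repeated structure.* Friedman's test is a repeated-measures test. What is missing is any between-group test that uses the earlier samples.
- *That the endotoxin conclusion rests on a group main effect.* Averaging over three samples would shrink a day-7 difference d to (0 + 0 + d)/3 = d/3, but the Protocol never names the main effect as the deciding test.
- *That power falls to about 40%.* The day-7 Mann-Whitney reaches 38–40% in the 0.9 SD scenarios only if Bonferroni is spread over three times. The Protocol does not define that family, and this is a separate multiplicity question.
- *That a difference at samples 1 or 2, or a fall within both arms, will be claimed as efficacy.* Nothing says so, and the trial is framed as between-group superiority.

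Lastly, the Protocol does not say whether sample 2 is taken before the envelope is opened. That it precedes placement of the medication is clear from the order of steps, and the point needs only that.

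**Conclusion.** The point holds as a matter of efficiency and clarity on a secondary outcome; the planned tests are not invalid. Two of the three endotoxin samples cannot carry a medication effect, testing the groups there serves no purpose, and the day-7 comparison leaves a relevant covariate unused.

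Under the central assumptions (14 per arm, 0.9 SD, correlations 0.5/0.5/0.3), ANCOVA gains about 71 − 63 = 8 points over the day-7 t-test and 71 − 58 = 13 over the interaction. Against the t-test, the range at 0.9 SD runs from 60 − 64 = −4 points at correlations of 0.1 to 88 − 64 = 24 points at an S2–S3 correlation of 0.7. When all correlations are 0.7, the interaction comes close to ANCOVA (89% against 92%) or matches it (94% each in the 1.0 SD series). These figures assume normal log values and an effect only at day 7. That samples 1 and 2 are uninformative about the medication needs no such assumption.

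**What to change.** In the Statistical analysis section:

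1. Make the between-group endotoxin analysis one ANCOVA of log endotoxin at day 7 on group, with log sample 2 as covariate, reported as a ratio of geometric means with a 95% CI. Use rank ANCOVA if the residuals are clearly non-normal.
2. Describe samples 1 and 2 by group, without between-group tests.
3. In the Friedman sentence, state three time points for endotoxin and keep four for postoperative pain.

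The cost is wording. The samples are already scheduled, and the planned software can fit the model. The covariate uses one degree of freedom, with negligible power loss if the correlation is near zero. The log scale also needs a stated rule for any zero or unquantifiable reading.
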